### Safety assessment

2.10

Any adverse events, including acupoint hematoma, infection, dizziness, and apostasies will be evaluated during the whole treatment by the researcher. If any severe adverse events occurring, acupuncture intervention will be ceased immediately and the principal investigator will be informed to take proper actions. 1 month will be followed up after the trial in case of subsequent adverse events.

### Data collection

2.11

All the study data will be recorded on the case report form (CRF) and any corrections made to the CRF must be personally signed and dated by the person responsible. All data will then be entered into a predesigned, password-protected electronic data set by 2 independent investigators who are blinded to group allocation. Double-checking of entered data will be performed by another researcher to ensure accuracy.

### Sample size calculation

2.12

The trial is designed to determine the role of auricular and body acupuncture in the consciousness recovery of patients with TBI and prove that auricular and body acupuncture is superior to conventional treatment. Therefore, GCS change will be used as an evaluation index. According to our previous pilot study, the change of GCS before and after treatment in the intervention group was shown to be 5.62 ± 1.41 (n = 8) and that in control group was 4.50 ± 1.85 (n = 8). Sample size was estimated using the following formula: 

where n represents the number of samples required, n = n_1_ + n_2_, *Q*_1_ = n_1_/n, Q_2_ = n_2_/n with a significance level (*α* = 0.05) of a 2-sided 2-sample *t* test and 80% power to detect a difference between the 2 groups. Thus, a total sample size of 80 patients will be recruited allowing for 10% of attrition, with 40 in each.

### Statistical analysis

2.13

SPSS 20.0 (IBM SPSS Statistics, IBM Corp, Somers, NY) will be used to analyze the data. Quantitative data will be presented as mean ± standard deviation. GCS Barthel and FuglMeyer scores will be conducted between the 2 groups by a superiority independent sample *t* test with a 95% confidence interval. The incidence of complications and adverse events will be compared by *χ*^2^ test. A mixed model procedure will be applied to compare longitudinal changes in MMN amplitude between the 2 groups. Any missing data will be replaced by the last measured value. For all analyses, *P* values of less than .05 will be considered statistically significant.

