#### Eligibility criteria: inclusion criteria

2.3.2

The inclusion criteria will be as follows.

1.Meet the diagnostic criteria for TBI;2.Aged 18 to 70 years old, male or female;3.Initial GCS score between 3 and 8 points on admission and lasted more than 2 weeks;4.Imaging (magnetic resonance imaging) head has no obvious shift, missing, large necrosis of brain structure change and obvious brain stem (not including pyramidal tract) or thalamic lesions, each lobe lesions range can not exceed 30% of the scope of 1 side of the brain;5.No primary consciousness disorder and limb functional activity disorder;6.Signed informed consent.

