#### Eligibility criteria: exclusion criteria

2.3.3

The exclusion criteria will be as follows.

1.DOC not induced by TBI;2.Clinical course more than 1 year;3.Combination of heart, liver or kidney failure endanger the safety of life at any time;4.Younger than 18 years or older than 70 years;5.Those who do not receive electroacupuncture therapy;6.Women with pregnancy and lactation.

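### Section 2.13 tests GCS scores by an unadjusted t test although the trial was sized on change in GCS; name change as the response and adjust for baseline

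*Protocol article*

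**What the plan says.** Section 2.13 (Statistical analysis) sets the primary GCS comparison and both secondary scales in one sentence: "GCS Barthel and FuglMeyer scores will be conducted between the 2 groups by a superiority independent sample" t test with a 95% confidence interval. It names no covariate and does not mention change from baseline. A mixed model is planned, but only for MMN amplitude.

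Section 2.12 (Sample size calculation) uses a different variable: "GCS change will be used as an evaluation index". Its inputs come from a pilot in which "the change of GCS before and after treatment in the intervention group was shown to be 5.62 ± 1.41", against 4.50 ± 1.85 in the control group, with 8 patients in each. The test is specified "with a significance level (*α* = 0.05) of a 2-sided 2-sample" t test with "80% power to detect a difference between the 2 groups". The result is 80 patients, 40 per arm, after allowing for 10% attrition.

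The abstract calls the primary outcome changes in GCS. Section 2.9 names the GCS itself as the primary endpoint and speaks of changes only for the secondary scales.

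On the patients, section 2.3.2 requires "Initial GCS score between 3 and 8 points on admission and lasted more than 2 weeks", and section 2.3.3 excludes "Clinical course more than 1 year". Section 2.4 describes computer-generated random numbers and names no stratification factor.

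**The concern.** A power statement belongs to one variable and one test. The SD of a change score and the SD of a follow-up score are different quantities, linked by the baseline SD and the baseline-to-follow-up correlation. If section 2.13 is applied literally to follow-up scores, the 80% power is a statement about another analysis.

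The second matter is efficiency. Every patient has a baseline GCS, and entry is open from just over 2 weeks to 1 year of clinical course. In the pilot the control group gained 4.50 points, about four times the 1.12-point difference the trial is sized to detect. Recovery without acupuncture is thus large relative to the target, and with 80 patients a chance difference in factors that predict recovery could matter. A t test on raw scores uses no baseline information. A t test on change uses it with a fixed weight of 1, whatever the data show. ANCOVA estimates the weight.

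**Working it through.** **Inputs.** From section 2.12: change 5.62 (SD 1.41) and 4.50 (SD 1.85), two-sided alpha 0.05, power 80%, 40 per arm, 10% attrition (36 per arm evaluable). Not in the documents, so assumed and varied: the baseline-to-follow-up correlation r and the SD of baseline GCS. All powers below are from the noncentral t distribution for a difference of 1.12. ANCOVA is approximated by using its residual SD in the same formula.

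**1. The plan's own figure.**
- Difference = 5.62 − 4.50 = 1.12.
- Pooled SD of change = √((1.41² + 1.85²)/2) = 1.645.
- Standardised effect = 1.12/1.645 = 0.681.
- Required n = 34.8, so 35 per arm; 35/0.9 = 38.9, so 39 per arm and 78 in total, against the stated 80.
- Power at 36 per arm = 0.81.

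The sample size therefore reproduces, and it rests on the SD of change.

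**2. Equal SDs at both visits.** The SD of change fixes the follow-up SD for each r: SD_raw = 1.645/√(2(1 − r)). The ANCOVA residual SD is SD_raw × √(1 − r²), so the ratio of ANCOVA variance to change-score variance is (1 + r)/2.

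| r | SD_raw | Power, raw score | Power, change | ANCOVA SD | Power, ANCOVA |
|---|---|---|---|---|---|
| 0.3 | 1.390 | 92% | 81% | 1.326 | 94% |
| 0.5 | 1.645 | 81% | 81% | 1.424 | 91% |
| 0.7 | 2.123 | 60% | 81% | 1.516 | 87% |

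Below r = 0.5 the raw-score test has more power than the change test; above it, less.

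**3. Equal SDs dropped.** Baseline GCS is confined to 3 to 8 and follow-up is not, so equal SDs are doubtful. Take a baseline SD (SDb) of 1.5 or 1.7 and solve 1.645² = SDb² + SDp² − 2·r·SDb·SDp for the follow-up SD (SDp). The slope on baseline is b = r × SDp/SDb.

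| SDb | r | SDp | b | Power, raw score | Power, change | Power, ANCOVA |
|---|---|---|---|---|---|---|
| 1.5 | 0.5 | 1.759 | 0.59 | 76% | 81% | 87% |
| 1.7 | 0.5 | 1.583 | 0.47 | 84% | 81% | 93% |
| 1.5 | 0.7 | 2.298 | 1.07 | 53% | 81% | 81% |
| 1.7 | 0.7 | 2.300 | 0.95 | 53% | 81% | 81% |

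When b is close to 1, ANCOVA and the change score are nearly the same analysis. The variance saving in the last two rows is below 0.5%.

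**4. Chance imbalance.** At 36 per arm the standard error of the baseline difference is SDb × √(2/36), which is 0.35 for SDb = 1.5 and 0.40 for SDb = 1.7. A raw-score comparison carries b times the imbalance into the treatment estimate; a change comparison carries (b − 1) times. For a one-standard-error imbalance at r = 0.5:
- SDb = 1.5: raw 0.59 × 0.35 = 0.21; change −0.41 × 0.35 = −0.14.
- SDb = 1.7: raw 0.47 × 0.40 = 0.19; change −0.53 × 0.40 = −0.21.

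That is roughly an eighth to a fifth of the 1.12 target (0.14/1.12 = 13%, 0.21/1.12 = 19%). At r = 0.7 the raw-score carry-over is about 0.38 points and the change-score carry-over almost nil.

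**The case against.** The strongest reply is that section 2.13 is loosely worded and means the test described in section 2.12. That section names GCS change and a two-sided two-sample t test, and the abstract agrees. The same sentence of section 2.13 also speaks of scores for Barthel and Fugl-Meyer, which section 2.9 says are assessed as changes. On this reading sizing and analysis match, the 81% stands, baseline is used by subtraction, and the raw-score powers do not apply. This reading is plausible, so a power shortfall is conditional and not shown. Section 2.9, which gives the GCS itself as the endpoint, keeps the text from settling the matter.

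It can also be said that an unadjusted t test on a randomised comparison is valid, and that covariates are often left to the analysis plan, which is not shown. The first part stands: neither bias nor type I error is at issue. The second stands only in part, because the protocol does not leave the method open; it fixes a t test and words it on scores.

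Two stronger readings are tempting. A reader might infer that the plan ignores baseline GCS altogether, or that a baseline imbalance passes in full into the treatment difference. The first is untrue if change is tested. The second would hold for the raw score only with a slope of 1. A reader might also infer that ANCOVA is certain to add power; step 3 shows cases with no gain over the change test. Finally, the article's silence on stratification does not show that randomisation is unstratified.

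**Conclusion.** The point holds as a mismatch of wording with a near-costless improvement attached. The tested variable in section 2.13 does not match the sizing variable in section 2.12, and the stated power belongs to change only.

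- If raw follow-up scores are tested, power at 36 per arm is about 92%, 81% and 60% at r = 0.3, 0.5 and 0.7 under equal SDs.
- If change is tested, power is 81% as designed. ANCOVA is as precise or more so: no gain when the slope on baseline is near 1 (81% at r = 0.7 with baseline SD 1.5 to 1.7), and a substantial gain at r = 0.5 with the same SDs (87% to 93%).

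These figures rest on the pilot SDs and on assumed values of r and baseline SD. Adjusting for time since injury is reasonable given the wide entry window, but its benefit cannot be put in numbers from the documents. The unadjusted test would not be wrong, so this is a recommended improvement to a valid analysis.

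**What to change.** In section 2.13, name change in GCS as the response, and word section 2.9 to agree with it and with the abstract. Analyse it by ANCOVA with treatment arm, baseline GCS and time since injury as prespecified terms, and report the adjusted difference with its 95% CI. Use the same model for Barthel and Fugl-Meyer, each with its own baseline. Keep the t test on change as a supportive analysis, since it is the one that matches the sample size calculation.

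The cost is wording only. Baseline GCS and time since injury are already needed to judge eligibility, so no new data or patients are required and the sample size can stay at 80. The change should be fixed before the analyst sees outcome data by arm.

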**Methods::**

Here, we conduct a study design and protocol of a randomized, blinded, controlled study to evaluate the efficacy and safety of electroacupuncture at auricular acupoints “heart” and “brainstem” combined with body acupuncture in the consciousness recovery of patients with TBI. A total of 80 patients with initial Glasgow coma scale score between 3 and 8 points will be recruited in the trial and randomized into intervention (combined application of auricular electroacupuncture and body acupuncture) group or control (conventional treatment) group. Patients in the intervention group will receive electroacupuncture at bilateral auricular acupoints “heart” and “brainstem” (4 points in total) combined with body acupuncture in addition to conventional treatment while patients in the control group will receive conventional treatment alone for 8 weeks. The primary outcomes are changes of Glasgow coma scale score and mismatch negativity of event-related brain potentials at baseline after 4 weeks after the final treatment and 4 weeks after the final treatment. The secondary outcome measures will be changes of Barthel and FuglMeyer scores at baseline after 4 weeks after the final treatment and 4 weeks after the final treatment. The safety will also be assessed by monitoring the incidence of adverse events and changes in vital signs during the study.

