**Discussion::**

Results from this trial will significantly support the application of auricular acupuncture and body acupuncture in the consciousness recovery of patients with severe TBI. If found to be effective and safe, auricular acupuncture combined with body acupuncture will be a valuable complementary option for comatose patients with TBI.

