### Conventional treatment in both groups

2.7

All the participants will accept conventional treatment, including the prescription of coma arousal and neuroprotective medicines. Details of conventional treatment used during the trial will be recorded, noting any change and the reasons.

Auricular electroacupuncture combined with body acupuncture in the intervention group.

In addition to conventional treatment, patients in the intervention group will receive both auricular point electroacupuncture and body acpuncture. Auricular point electroacupuncture manipulation was as follows: Following disinfection of skin with 75% alcohol, bilateral auricular acupoints “heart” and “brainstem”^[19]^ (4 points in total) will be stimulated using disposable and stainless needles (13 mm long and 0.25 mm in diameter, Suzhou Huanqiu Acupuncture Medical Appliance, Suzhou, China) inserted to a depth of 2 mm, and connected to an electrical stimulator (SDZ-V EA; Huatuo, Suzhou, China) with a frequency of 2/10 Hz and current of 1 mA. Body acupuncture manipulation was as follows: After disinfection, GV26^[20]^ was inserted towards the nose at a depth of 10 mm while bilateral PC6^[20]^ and SP6^[20]^ was perpendicularly inserted at a depth of 20 mm by disposable and stainless needles (40 mm long and 0.30 mm in diameter, Suzhou Huanqiu Acupuncture Medical Appliance). The needle will be manipulated using twirling, lifting, thrusting, and mild reinforcing-reducing methods to promote Qi. Eye moisture or the presence of tears will be used as an indicator of Qi arrival since patients are not able to express their feelings. Acupuncture will be restrained for 30 minutes, once daily, 5 times a week and lasted for 8 weeks. The location of acupoints applied was shown in Table 1.

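### The between-arm adverse-event test covers acupoint hematoma and dizziness, which the two arms cannot show on equal terms; report these separately and add risk differences with confidence intervals

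*Protocol article*

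**What the plan says.** Section 2.13 (Statistical analysis) gives the only comparative rule for safety events: "The incidence of complications and adverse events will be compared by" a chi-square test. The same section applies one threshold to all analyses: P "values of less than .05 will be considered statistically significant".

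Section 2.10 (Safety assessment) gives an open list of what is counted: "Any adverse events, including acupoint hematoma, infection, dizziness, and apostasies will be evaluated during the whole treatment by the researcher".

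Three other places bear on who can have or report these events:
- Abstract, Methods: "patients in the control group will receive conventional treatment alone for 8 weeks". Section 2.6 agrees, and there is no sham needling.
- Section 2.3.2 (inclusion criteria): "Initial GCS score between 3 and 8 points on admission and lasted more than 2 weeks".
- Section 2.7, on how the response to needling is judged: "since patients are not able to express their feelings".

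The abstract's discussion looks ahead to a conclusion on safety: "If found to be effective and safe". The article gives no expected adverse-event rate and no power for safety.

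**The concern.** A between-arm test is informative about relative risk when both arms can have the event and both have the same chance of its being recorded. Two of the named events fail one of these conditions.

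- **Acupoint hematoma.** The control rate is zero by design. A null hypothesis of equal rates could be true only if needling never caused a hematoma. One case already settles that, so the useful quantity is how often it happens, and a chi-square p-value does not give it.
- **Dizziness.** A patient who cannot communicate cannot report it. If the intervention restores consciousness in more patients, more of them can complain of dizziness, and the treatment looks less safe because it works. A treatment that does not help would gain no such penalty.

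At stake is the safety half of the trial's conclusion. A significant difference in dizziness could reflect who was awake, and a non-significant one leaves a sizeable excess risk open.

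**Working it through.** **1. Inputs.** From the article: 80 patients, 1:1, 40 per arm, 10% attrition (36 per arm if all of it occurs), threshold P < .05, chi-square test. All event rates and reporting proportions below are assumptions, because the article gives none.

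**2. Where 40 per arm comes from.** Section 2.12 bases it on GCS change: "a total sample size of 80 patients will be recruited allowing for 10% of attrition, with 40 in each". The pilot difference is 5.62 − 4.50 = 1.12. The SD is √((1.41² + 1.85²)/2) = 1.645, so the effect size is 1.12/1.645 = 0.681. A two-sided t test at 5% with 80% power needs 34.8, so 35 per arm. Allowing for attrition, 70/0.90 = 77.8, so 78, close to the stated 80. The size was set for GCS, not for safety.

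**3. Method.** Let X be the intervention count and Y the control count, independent Binomial(40, p₁) and Binomial(40, p₀). The chance of significance is the sum of Pr(X = x)·Pr(Y = y) over all tables with Pearson P < .05 (no continuity correction).

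**4. Acupoint hematoma (p₀ = 0 by design).**

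| Assumed true rate in needled arm | Chance that P < .05 (40 per arm) | 36 per arm |
|---|---|---|
| 5% | 14% | 10% |
| 10% | 58% | 49% |
| 20% | 97% | 95% |

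The null is false in every row, and at a 5% rate the test misses this 86% of the time. Three hematomas v none gives P = 0.078 and four v none gives P = 0.040, although either count shows that the risk is above zero.

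**5. Dizziness.** Assume the same true rate of 30% in both arms. The recorded rate is the true rate times the proportion able to report.
- 60% v 30% able to report: 0.30 × 0.60 = 18% v 0.30 × 0.30 = 9%. Significant about 23% of the time (21% at 36 per arm), almost always with the intervention arm higher.
- 45% v 30% able to report: 13.5% v 9%. Significant about 11% of the time.
- 30% v 30% able to report: 9% v 9%. Significant 5.9% of the time.

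The excess over the last line is due entirely to who can report.

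**6. What a p-value leaves open at 40 per arm.**
- Power for a true 15% v 5% is about 35% (32% at 36 per arm).
- With 0 events in 40, the exact 95% upper limit is 1 − 0.025^(1/40) = 8.8%.

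**The case against.** Several stronger readings are tempting, and the documents do not support them.

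- **A reader might infer that counts will be sparse and chi-square therefore invalid.** No event rate is given, the list is open, and the test also covers complications in severely injured patients, so overall counts may be large. Even at low rates the test behaves acceptably: at 40 per arm its exact type I error is 0.7% at a 2% rate, peaks at 5.9% near 9%, and is 5.1% at 20%.
- **A reader might infer that Fisher's exact test is needed.** The two tests do part company on some tables (4 v 0 gives P = 0.040 by chi-square and 0.116 by Fisher), but this mainly reflects Fisher's conservatism: its size is 0.4% at a 5% rate. Using Fisher whenever an expected count is below 5 would cut power for 15% v 5% from 35% to 22%. That is a real loss when looking for harm.
- **A reader might call a difference driven by hematomas a false signal.** With needle-site events in 20% of the needled arm and a 5% background in both arms (24% v 5%), a pooled test is significant 73% of the time. But acupuncture is added to conventional treatment, so hematomas it causes are real extra harm and detecting them is correct. Separating them makes the result interpretable; it does not remove an error.
- **A reader might infer that the plan treats P > .05 as proof of safety.** No section says so, and vital signs are also assessed.

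Two further points stand in part. The remark that patients cannot express their feelings is made about needling response, and section 2.10 has the researcher evaluate events. The inclusion criterion nevertheless makes self-report doubtful at entry, and dizziness has few signs that an observer could record instead. Also, a condensed article may leave tabulation by event type and confidence intervals to documents not shown. The point therefore rests on the stated test combined with the stated events, not on what is absent.

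**Conclusion.** The concern holds in a limited form and is minor. The article applies a between-arm significance test to a list containing one event that controls cannot have and one whose recording depends on the efficacy outcome. For those two events the p-value does not compare risk on equal terms.

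For dizziness, the chance of a significant difference with no true difference is about 23% under the wider reporting gap assumed above and about 11% under the narrower one. Both depend on an assumed 30% true rate and on reporting proportions that the article does not give. The direction is firmer than the size: if the treatment wakes more patients, the recorded excess falls on the intervention arm.

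For events that both arms can have, the planned test can stay, but with 40 per arm it needs an interval beside it to say how much harm remains possible.

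**What to change.** Keep the planned chi-square test where both arms can have the event, and amend sections 2.10 and 2.13 as follows:

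1. Report acupoint events (hematoma, infection at a needle site) as incidence with an exact 95% CI in the intervention arm only.
2. For events possible in both arms, including infection other than at needle sites, give the risk difference with a 95% CI beside the planned test.
3. Tabulate symptoms that need self-report, such as dizziness, with the number of patients able to report in each arm, and do not base a safety difference on their crude between-arm test.
4. Base any statement on safety on the intervals, not on a p-value alone.

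The cost is a few sentences, slightly more tabulation and fewer formal tests. Event data are already collected. Ability to report has to be recorded or derived at the assessments; GCS is already measured and may serve if the rule is fixed before unblinding.

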### Quality control

2.14

Before the trial, all the acupuncturists nurses and assessors will be trained strictly in order to guarantee homogeneity in the measurement data and ensure high-quality data results. The training content will include study protocol, diagnosis, inclusion and exclusion criteria, recording method of CRF, the location of the acupoints, acupuncture operation techniques, disposal of bleeding. All the study data will be recorded on the CRF. Dropouts and withdrawals from the study will be recorded in detail based on the intervention and follow-up periods. Data will be uploaded and verified by other 2 researchers who were not involved in the trial. This trial will be monitored by the Scientific Research Department of GuangDong Second Hospital of Traditional Chinese Medicine every 1 week.

